**Table 1 Tab1:** **List and timeline of assessments for the Healthy Transition Trial (HTT)**

	Screening	Baseline	2 months	6 months	12 months
Sociodemographic information	YES	-	-	-	-
Patient Health Questionnaire (PHQ-9)	YES	YES	YES	YES	YES
Five-year menstrual history	YES	YES	YES	YES	YES
Gynaecological history	YES	YES	YES	YES	YES
Past history of severe mental disorder	YES	-	-	-	-
Severe medical illness (for example, metastatic cancer)	YES	-	-	-	-
Medical morbidities checklist	YES	YES	YES	YES	YES
Alcohol Use Disorders Identification Test	YES	YES	YES	YES	YES
Self-reported hearing or visual impairment	YES	-	-	-	-
Self-reported English fluency	YES	-	-	-	-
Contact details for general practitioner	YES	-	-	-	-
Hospital Anxiety and Depression Scale (HADS)	-	YES	YES	YES	YES
Mini-Neuropsychiatric Interview	-	YES	YES	YES	YES
Short-Form Health Survey, SF-12	-	YES	YES	YES	YES
Menopause Rating Scale (MRS)	-	YES	YES	YES	YES
Food Frequency Questionnaire	-	YES	YES	YES	YES
Prescription and non-prescription medications	-	YES	YES	YES	YES
Self-reported weight (Kg) and height (cm)	-	YES	YES	YES	YES
Smoking, alcohol and physical activity	-	YES	YES	YES	YES

### Sample size

Data from the Australian National Survey suggest that the prevalence of clinically significant depression is 14% around the MT and about 6% immediately before the MT or after the menopause [5]. An effective intervention should decrease the prevalence of depression amongst these women from 14% to 6%, which would represent an absolute risk reduction of 8%. The expected number of women that we will need to treat to prevent one person developing depression is 13. A sample size of 300 women (1:1 allocation) will give the study 80% power to declare such a difference as statistically significant (alpha = 5%). These numbers take into account a loss of 40 women during the course of the study.

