### Women undergoing the menopausal transition require a targeted health promotion intervention

The MT affects all ageing women with intact ovaries. Marked physiological and psychosocial changes characterise this unique period of a woman’s life, including symptoms such as hot flushes and night sweats, remodelling of body shape, shifting social roles (for example, children moving away from home), and onset of chronic illnesses (such as diabetes and hypertension). All these factors may interact to facilitate the development of depressive symptoms during the MT. As depression and poor lifestyle practices in mid life have been associated with poor health outcomes in older age [11, 27–29], developing health promotion interventions that are relevant to women in the MT seem not only desirable, but a necessity.

In summary, published observational data suggest that women undergoing the MT are at increased risk of clinically significant depressive symptoms and highlight numerous health and behavioural factors that might potentially mediate such increased risk. We have designed a health promotion intervention that seeks to address these risk factors systematically and to enhance behaviours associated with good mental health outcomes. More specifically, this study will aim to address the following:determine the efficacy of a telephone-medicated health promotion intervention, compared with usual care, in decreasing the 12-month incidence of clinically significant symptoms of depression in women undergoing the menopausal transition who do not have clinically significant symptoms of depression or mental disorders at the time of entry into the study,determine the efficacy of a telephone-mediated health promotion intervention in decreasing the 12-month incidence of major depressive episodes in women undergoing the menopausal transition, compared to usual care,measure the effect of a telephone-mediated health promotion intervention in decreasing the severity of depressive symptoms over 12 months compared to usual care,ascertain the prevalence of clinically significant symptoms of depression among community-dwelling Western Australian women undergoing the menopausal transition.

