Volunteers will be excluded from participating for the following reasons:they disclose a history of gynaecological surgery that compromises the ability to assign menopausal status (that is, hysterectomy, bilateral oophorectomy, or endometrial ablation);they report an illness that may impact upon 12-month survival (for example, metastatic cancer);they receive medical treatment or undergo medical procedures that hinder ability to assign menopausal status (hormone therapy, hormonal intrauterine devices, contraceptive implants, patches or medications);there is evidence of clinically significant depressive symptoms (PHQ 9 ≥ 15) or major depressive episode at the time of assessment;there is evidence of concurrent alcohol abuse or dependency (AUDIT ≥15);they report past or current history of schizophrenia, delusional, schizoaffective or bipolar disorder;there is evidence of significant hearing impairment that may compromise telephone communication;they are not fluent in written or spoken English;they plan to leave Western Australia within the following 12 months;they report active suicidal ideation;they do not have an active GP or do not consent to the research team liaising with their GP throughout the course of the study; orthey fail to provide written informed consent.

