## Discussion

Our strategy to recruit participants using the electoral roll aims to increase the external validity of the results of this study and offers the additional flexibility of increasing the number of people approached, if necessary. We have an established record of success for recruiting participants into large community-based trials and of collaborative work with primary care physicians, such as the Health In Men Study [40] and the Depression and Early Prevention of Suicide in General Practice (DEPS-GP) project [26]. We are therefore confident that our recruitment strategy will yield the required number of participants.

We have also designed an intervention that takes into account the reality of health care delivery in Australia, so that the study activities can later be incorporated into normal clinical practice through existing Medicare Benefits Schedule. Sustainability requires evidence of efficacy and of cost-effectiveness to lead to a commitment to long-term implementation. This study aims to establish evidence of efficacy. Furthermore, we broadly estimate that the total cost of the intervention per participant will be about A$412: $50 x 8 for health coaching + $2 × 6 for correspondence. We anticipate that 13 women will need to be treated for one to benefit, which would result in a total cost of about A$5,500 to avoid one case of depression. The estimated annual cost of depression per patient in Australia is approximately A$17,000 (considering an extremely conservative 30% increase in costs since the publication of Australian estimates in 2003) [41]. This would result in a minimum net gain of $11,500 per year for every 13 women treated (savings in other health areas have not been taken into account, so savings could be even greater). These preliminary calculations indicate that the intervention will be cost-effective if the expected benefits are confirmed.

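### The sample size plans a 12-month onset endpoint on survey prevalences (14% and 6%), and no incidence is given to support the power or the NNT of 13

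*Protocol article*

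**What the plan says.** The Sample size section cites a national survey in which "the prevalence of clinically significant depression is 14% around the MT and about 6% immediately before the MT or after the menopause". It then says "An effective intervention should decrease the prevalence of depression amongst these women from 14% to 6"%, "which would represent an absolute risk reduction of 8"%. From this it derives the NNT ("The expected number of women that we will need to treat to prevent one person developing depression is 13") and the power: "A sample size of 300 women (1:1 allocation) will give the study 80% power to declare such a difference as statistically significant (alpha = 5"%). The loss of 40 women is said to be already allowed for.

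The aims, at the end of the Background, concern efficacy "in decreasing the 12-month incidence of clinically significant symptoms of depression in women undergoing the menopausal transition", in women free of clinically significant symptoms at entry. Outcomes and study measures defines the primary endpoint as onset over 12 months, assessed at 8, 26 and 52 weeks. The Participants section admits only women with PHQ-9 below 15. It excludes those with PHQ-9 of 15 or more "or major depressive episode at the time of assessment".

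The Discussion reuses the NNT ("We anticipate that 13 women will need to be treated for one to benefit") to reach about A$5,500 per case of depression avoided.

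**The concern.** A prevalence counts women who have the condition, whenever it began. The trial counts women who develop it during a year, having been free of it at the start. By design, the prevalence of the endpoint condition at entry is zero in both arms, so there is no 14% at baseline to bring down to 6%. The Sample size section moves from one concept to the other within a paragraph: it starts with prevalence and ends with the number treated to prevent one woman developing depression. It shows no link between the two.

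The intervention rate has a similar difficulty. The 6% is the survey figure for women outside the transition. Using it for the treated arm sets the effect equal to the whole transition-related excess, a relative risk of 6/14 = 0.43.

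The control rate drives everything downstream: the absolute reduction, the power, the NNT and the cost case. If it is the wrong kind of rate, none of these can be relied on as a description of what the trial can show.

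**Working it through.** **Inputs from the article.** Rates of 14% and 6%; 300 women, 1:1; 40 lost, so 260 evaluable, or 130 per arm (Sample size). Two-tailed 5% (Statistical methods). A$412 per participant (Discussion).

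**Step 1: the article's own figures.**

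NNT = 1/(0.14 − 0.06) = 1/0.08 = 12.5, which rounds to 13. This is reproduced. The cost is 13 × 412 = A$5,356, given as about A$5,500.

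Power, by the pooled-variance z-test with n = 130 per arm:

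Φ{[d − 1.96 √(2p̄(1−p̄)/n)] / √([p1(1−p1) + p2(1−p2)]/n)}

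With d = 0.08 and p̄ = 0.10, the null standard error is √(0.18/130) = 0.0372 and the alternative one is √(0.1768/130) = 0.0369. Then (0.08 − 0.0729)/0.0369 = 0.19, and the power is 57.6%. The exact power of the Pearson test is 58.9%. With 150 per arm and no loss, the power is 63.8%. The stated 80% needs 220 per arm (440 evaluable). Among the variants tried, only a one-sided test with 340 evaluable women comes near 80% (79.4%), which conflicts with the two-tailed rule and with recruiting 300. This shortfall exists even if 14% and 6% are accepted, so it is a separate matter from the present point.

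**Step 2: what the control rate does to the plan.** The article gives no 12-month incidence in eligible women, so the control incidence p1 below is an assumption. The relative risk is held at 6/14, also an assumption, so p2 = p1 × 6/14 and NNT = 1/(p1 × 8/14) = 1.75/p1. Cost per case avoided is A$412 × NNT.

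| Control incidence | Power, 130 per arm | NNT | Evaluable women for 80% power | Cost per case avoided |
|---|---|---|---|---|
| 4% | 20% | 43.8 | 1,666 | about A$18,000 |
| 6% | 28% | 29.2 | 1,094 | about A$12,000 |
| 8% | 35% | 21.9 | 808 | about A$9,000 |
| 10% | 43% | 17.5 | 636 | about A$7,200 |
| 14% | 58% | 12.5 | 440 | about A$5,150 |
| 20% | 75% | 8.8 | 292 | about A$3,600 |

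**Step 3: a different effect assumption.** If the intervention rate is instead fixed at 6%, a control incidence of 10% gives 22% power and an NNT of 25, and 20% gives 92% and an NNT of 7.1. The results depend on both assumptions, and the article supports neither on the incidence scale.

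**Step 4: direction.** Removing current cases at entry pulls the 12-month rate below a prevalence. Three features push it up. Onset is counted at three assessments over a year, with the MINI intended to pick up episodes between visits. Women with PHQ-9 of 5 to 14 are enrolled and are described under Randomisation and blinding as being at greater risk. Past depression is not an exclusion, and the Background says it raises the risk of recurrence nearly fivefold. The article gives no figure with which to net these off.

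**The case against.** The strongest objection is that the direction is unproven. A reader might infer that onset in screened women must be below 14%, and so that the trial is weaker than planned. The documents do not support that: for the reasons in step 4, the rate could be higher, and at 20% the power is better than at 14%.

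A reader might also attribute the whole fall from 80% to, say, 43% at 10% to the wrong kind of rate. Only the part from 58% to 43% belongs here; the part from 80% to 58% is the arithmetic fault. Likewise, the control incidence of about 22% needed for 80% power with 130 per arm mainly reflects the small sample, since with 440 evaluable women 14% would suffice.

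It is tempting to say that the survey's 14% are exactly the women screened out. The article does not say how the survey defined clinically significant depression, or over what period, so equating it with PHQ-9 of 15 or more is an assumption.

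The relative risk of 0.43 can fairly be read as a target. The wording says what an effective intervention should achieve, and an ambitious target is a design judgement. The cost passage is already hedged as broad and preliminary, and the NNT is to be recalculated from trial data.

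These objections limit the point but do not remove it. Prevalence may serve as a proxy if it is named and justified as one. Here the gap between two prevalences is presented directly as the trial's absolute risk reduction. Nor is this only something left to a fuller protocol: the stated rationale does not fit the article's own eligibility criteria and endpoint.

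**Conclusion.** The point holds in limited form. The planning rates are prevalences, the endpoint is 12-month onset in women without the condition at entry, and nothing in the article connects the two. The 8-point reduction, the power and the NNT of 13 are therefore unsupported; they are not shown to be wrong in a known direction.

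The sensitivity is large. With a relative risk of 6/14, 130 evaluable per arm and two-sided 5%, moving the assumed control incidence from 6% to 20% takes power from 28% to 75% and the NNT from 29 to 8.8. At 4% the cost per case avoided, about A$18,000, would exceed the A$17,000 annual cost of depression quoted in the Discussion. The control incidences and the constant relative risk are illustrative assumptions. This should be corrected, because the trial's headline planning figures depend on it.

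**What to change.** - State a 12-month incidence for women eligible at entry (PHQ-9 below 15, no current major depressive episode), with its source or the reasoning that leads to it from the survey prevalence.
- Present the reduction to 6% as a target effect, not as an estimate of what the intervention does.
- Replace the single power and NNT with a short table over a range of control incidences, such as the one above, and give the cost per case avoided over the same range.
- Do not simply write incidence in place of prevalence beside 14% and 6%. That would relabel an unsupported figure and hide the problem.
- Report separately that, even at 14% versus 6%, the stated design gives about 58% power and not 80%. Changing the source of the rate will not repair that.

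The text change costs a few sentences and a small table, and some published figures may become less favourable. If the justified incidence calls for more women, the cost is larger recruitment. The trial is still recruiting, and the Discussion says that more women can be approached if necessary.

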## Methods/Design

### Trial design

The Healthy Transition Trial (HTT) is a randomised, parallel, controlled trial of a telephone-driven health promotion intervention designed to prevent the onset of clinically significant symptoms of depression during the MT. The allocation ratio will be 1:1.

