### Outcomes and study measures

The onset of clinically significant symptoms of depression or of a major depressive episode over 12 months represents the primary endpoint of interest of this trial. We will use the Patient Health Questionnaire (PHQ-9) to establish the presence of clinically significant symptoms of depression. The PHQ-9 is the self-administered depression module of the PRIME-MD diagnostic instrument for common mental disorders. It consists of nine questions about how often the respondent has been bothered by depressive symptoms during the past two weeks, and each item can be scored 0 (not at all), 1 (several days), 2 (a week or more) or 3 (nearly every day). The nine items are as follow: (a) decreased interest or pleasure, (b) low mood, (c) sleep disturbance, (d) lack of energy, (e) disturbed appetite, (f) feelings of failure or guilt, (g) poor concentration, (h) psychomotor disturbance, and (i) suicidal thoughts. The scale has well-established psychometric properties and face-validity, with scores of 15 or greater indicating the presence of clinically significant symptoms of depression that warrant treatment [32]. Endpoints will be collected at 8, 26 and 52 weeks. Another primary endpoint of interest is the onset of a DSM-IV-TR major depressive episode during follow-up, as ascertained by the Mini-Neuropsychiatric Interview (MINI) 8, 26 and 52 weeks after the baseline assessment [33]. The MINI can take between 15 and 45 minutes to complete and it will allow us to investigate the presence of depressive episodes that may have occurred between assessments [34]. Only women who score 15 or more on the PHQ-9 will undergo assessment with the MINI.

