### Statistical methods

Data analysis will be blind to group assignment. We will use descriptive statistics to summarise study measures and will compare their distribution at the baseline assessment for the intervention and control groups using t-tests, Mann-Whitney tests and Pearson’s chi-square statistic. Analyses of outcomes will be intention-to-treat (ITT) and will be ascertained using xtlogit models for binary outcomes (for example, developed a depressive episode during follow up: yes/no. Effect expressed as odds ratio and respective 95% confidence limits) and multilevel mixed-effects linear regression (xtmixed models) to analyse changes in scale scores over time (for example, changes in HADS scores - effect estimate expressed as mean change of score from baseline). We will also use contingency tables to calculate the number needed to treat (NNT) for one person to benefit from the intervention, taking into account the number of participants who may be lost during follow up. The NNT is the reverse of the absolute risk reduction. Alpha will be set at 5% and all statistical tests will be two-tailed. Data from this trial will determine if the intervention causes benefit, harm or neither.

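### The stated 80% power does not follow from the plan's own inputs: 300 women with 40 lost give about 58% power for 14% versus 6%

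*Protocol article*

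**What the plan says.** The Sample size section takes its rates from a national survey, in which "the prevalence of clinically significant depression is 14% around the MT and about 6% immediately before the MT or after the menopause". It then says that an effective intervention "should decrease the prevalence of depression amongst these women from 14% to 6%, which would represent an absolute risk reduction of 8" percentage points. From this it concludes that "A sample size of 300 women (1:1 allocation) will give the study 80% power to declare such a difference as statistically significant", at an alpha of 5%, and closes with "These numbers take into account a loss of 40 women during the course of the study".

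The other inputs are stated elsewhere in the article:

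- Trial design: "The allocation ratio will be 1:1".
- Statistical methods: "Alpha will be set at 5% and all statistical tests will be two-tailed".
- Outcomes and study measures, where the endpoint is a yes/no event per woman: "The onset of clinically significant symptoms of depression or of a major depressive episode over 12 months represents the primary endpoint of interest".

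**The concern.** Two proportions as low as 14% and 6% usually need more than 200 women per arm for 80% power at two-sided 5%. The plan expects to analyse about 130 per arm, so the claim looked too favourable by a wide margin.

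This paragraph is the article's only justification for the size of the trial. If the power is really below 60%, a trial in which the intervention works exactly as assumed would still fail to reach significance about four times in ten. Statistical methods ends by saying that the data will settle whether the intervention helps, harms or does neither. At such power a non-significant result cannot establish the third of these, and a reader who trusts the 80% could take it that way.

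**Working it through.** **Inputs, all from the protocol article**

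- Control rate p1 = 0.14, intervention rate p2 = 0.06, difference 0.08 (Sample size).
- 300 randomised 1:1, so 150 per arm (Sample size; Trial design).
- Loss of 40 women (Sample size): 300 − 40 = 260, a loss of 40/300 = 13.3%. An equal split, giving 130 per arm, is an assumption; the article states only the total.
- Two-sided 5%, so z = 1.960 (Statistical methods).

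The effect size is internally consistent: 1/0.08 = 12.5, which rounds up to the stated number needed to treat of 13. The problem lies in the link between sample size and power.

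**Attempt to reproduce the 80%**

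Pooled two-proportion formula, with mean rate p̄ = (0.14 + 0.06)/2 = 0.10:

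power = Φ{ [d − z·√(2p̄(1−p̄)/n)] / √([p1(1−p1) + p2(1−p2)]/n) }

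Here 2p̄(1−p̄) = 0.18, and p1(1−p1) + p2(1−p2) = 0.1204 + 0.0564 = 0.1768.

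- n = 130: (0.08 − 1.960 × 0.03721)/0.03688 = 0.192, so power = **57.6%**.
- n = 150 (no loss): (0.08 − 1.960 × 0.03464)/0.03433 = 0.353, so power = **63.8%**.

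Neither is near 80%.

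**Sample size that 80% needs**

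n = [1.960·√0.18 + 0.842·√0.1768]² / 0.08² = (0.8315 + 0.3539)²/0.0064 = 219.6, so 220 per arm and 440 analysed. At the plan's loss rate, 440/(260/300) = 507.7, about 508 randomised. With a continuity correction the need is 243.9, so 244 per arm.

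**Does another common method give 80%?**

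| Method | 130 per arm | 150 per arm |
|---|---|---|
| Pooled normal, two-sided | 57.6% | 63.8% |
| Unpooled normal, two-sided | 58.3% | 64.4% |
| Arcsine, two-sided | 59.2% | 65.4% |
| Log odds ratio, two-sided | 55.3% | 61.3% |
| Continuity-corrected, two-sided | 49.3% | 56.3% |
| Pearson chi-square, exact enumeration, two-sided | 58.9% | 64.9% |
| Fisher exact, two-sided | 50.2% | 58.3% |
| Pooled normal, one-sided 5% | 69.5% | 74.9% |
| Arcsine, one-sided 5% | 70.8% | 76.2% |

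The most favourable entry, one-sided with no loss, is still almost 4 points short and contradicts the two-tailed rule. At 130 per arm the pooled formula reaches about 80% only if the two-sided alpha is raised to 20% (81.0%).

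**What the planned sample can detect**

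Holding controls at 14% and solving for 80% power, two-sided 5%:

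- 130 per arm: intervention rate 4.1%, a reduction of 14 − 4.1 = 9.9 points.
- 150 per arm: intervention rate 4.6%, a reduction of 9.4 points.

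**The case against.** The best defence is repeated measurement. Endpoints are collected at 8, 26 and 52 weeks, binary outcomes are to be analysed with a panel logistic model, and the Sample size section speaks of prevalence rather than incidence. Suppose 14% versus 6% held at each of three visits, with within-woman correlation ρ. Three visits then carry the information of n·3/(1+2ρ) women per arm. Setting this equal to 219.6 with n = 130 gives 1+2ρ = 390/219.6 = 1.776, so ρ = 0.39. With all 150 per arm it gives 1+2ρ = 450/219.6 = 2.049, so ρ = 0.52. A correlation at or below these values would bring the power to 80% or more.

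It follows that the table above covers single-comparison methods only, and that a longitudinal calculation could in principle reach the figure. This does not rescue the stated claim. The Sample size section mentions no repeated-measures gain, no correlation and no difference at each visit. The endpoint is onset over 12 months, and the example given for the logistic model is one yes/no result per woman over follow-up.

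Two smaller points are fair. The 130 per arm figure assumes equal loss, but the 63.8% at 150 per arm does not, and it already contradicts 80%. The article also does not say outright that a non-significant result will be read as no effect, so that risk is possible rather than certain.

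It is no defence that an article condenses a fuller protocol. The article states a complete set of inputs and a result that does not follow from them, so this is not a complaint about missing detail.

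**Conclusion.** The concern holds. On the article's own inputs, power for 14% versus 6% is about 58% with 260 women analysed and about 64% with all 300, against a stated 80%. The shortfall is about 22 points (80 − 57.6) in the planned case. The chance of missing a true effect of the assumed size is about 42% (100 − 57.6), roughly twice the 20% implied. The analysed sample would have to be 440 rather than 260.

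The conclusion takes the 14% and 6% at face value, uses one binary outcome per woman and, for the 58% only, assumes equal loss between arms. It does not depend on the choice of two-proportion formula, on one- or two-sided testing, or on how losses are handled. This must be fixed because the trial relies on the figure and the error is far larger than rounding.

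**What to change.** Correct the Sample size paragraph. Suggested wording: *With 300 women randomised 1:1 and 40 lost, about 260 (130 per arm, assuming equal loss) will be evaluable. At a two-sided 5% level this gives about 58% power to detect a fall from 14% to 6%. With 14% in the control group, the reduction detectable with 80% power is about 10 percentage points (to about 4%).*

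The Discussion has no power statement at present. Add a sentence there, with a matching one beside the closing claim in Statistical methods, saying that a non-significant result will be described as inconclusive and read from the confidence interval.

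If the 80% came from a repeated-measures calculation, the authors should instead state it in full, with the per-visit rates and the assumed correlation, and reconcile it with an endpoint defined as onset over 12 months.

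The correction costs wording only, and the stated power becomes less favourable. It requires no extra enrolment. If the sponsor wants to keep 80% power for 14% versus 6%, about 508 women would have to be randomised at the same loss rate. Trial status says recruitment is still open, and the Discussion says more people can be approached, so that choice may still be available.
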